### 2.8. Data Collection and Management

Upon enrollment, each participant will be assigned a unique study ID to ensure pseudonymization of personal data. The data in this trial will be collected using traditional print-based case report forms. All data entries will be manually transcribed into the electronic system by trained study personnel. Double data entry will be employed to minimize transcription errors and ensure accuracy. The data storage is achieved using an electronic data capture system (REDCAP) which is HIPAA-compliant and allows storage of data in password-protected files in the cloud. Data acquired in paper form are kept in locked files at the respective study site. Only project staff will have access to the trial dataset. Participants who discontinue PAP therapy or deviate from the protocol will remain in the analytical sample, and all data collected up to the time of discontinuation, including cognitive, clinical, and physiological measures, will be included in the analyses.

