## Abstract

Obstructive sleep apnea (OSA) is the most common sleep-related breathing disorder and is increasingly recognized as a contributor to cognitive decline and a potential risk factor for neurodegeneration. Previous studies have also identified various associated comorbidities such as vascular dysfunction, metabolic alterations, and neuroinflammatory changes. Positive airway pressure (PAP) therapy has been associated with cognitive improvement in some studies, but its long-term effects on cognitive function remain uncertain. This study employs a prospective, observational, longitudinal cohort design to examine longitudinal associations between disease severity, PAP therapy and cognition. Additionally, we aim to examine the relationships between cognitive dysfunction, brain structure and associated OSA-related risk factors. A total of 100 eligible participants with mild to severe OSA will be recruited. All participants will undergo comprehensive assessments at baseline and after 12 months, including neurological, pulmonary, and ear, nose and throat clinical examinations, polysomnography, neuropsychological testing, brain magnetic resonance imaging with volumetry, anthropometric measurements, blood and saliva sampling for the assessment of the selected laboratory parameters, gut microbiome analysis, and evaluation of endothelial function and baroreflex sensitivity. This study may improve understanding of how PAP therapy and OSA-related pathophysiological processes influence cognitive outcomes.

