### 2.5. Outcome Measures

#### 2.5.1. Primary Outcome Measures

##### Cognitive Function

The primary outcome of the study is cognitive function assessed by a comprehensive neuropsychological battery. Primary cognitive outcomes will be derived from test performance across the main cognitive domains including memory, executive functions, attention, language, and visuoconstructional abilities. Cognitive performance will be evaluated both cross-sectionally at baseline, to characterize the prevalence, severity, and pattern of cognitive deficits in patients with OSA, and longitudinally as change in cognitive performance from baseline to 12 months. PAP therapy adherence will be treated as an exposure variable in analyses of longitudinal cognitive change.

To improve comparability across tests and reduce measurement variability, standardized z-scores will be calculated for each neuropsychological measure and subsequently aggregated into domain-specific composite scores. In addition to statistical significance, cognitive outcomes will also be evaluated for clinical relevance. Clinically meaningful improvement will be defined as a change greater than 1 standard deviation (SD) from baseline in domain-specific scores or a shift from impaired to normative performance range (e.g., from ≤5th percentile to >15th percentile) [22]. This ensures that changes in test performance reflect not only statistical but also functional significance.

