#### 2.5.3. Exposure Variables of Interest

##### PAP Therapy and Adherence to Treatment

The gold standard treatment of moderate/severe OSA is positive airway pressure (PAP) therapy, which works by holding the airway open using a pneumatic splint. There is evidence to suggest that compliant PAP therapy use can have beneficial effects on some of the consequences of this disorder. Adherence to the treatment will be measured through an adherence tracking system using smart memory cards, which will report all needed parameters. Adherence will be primarily analyzed as a continuous variable (e.g., average hours of use per night) to capture potential dose–response relationships with cognitive outcomes. In addition, secondary analyses will examine adherence as a categorical variable using standard criteria to classify participants as adherent or non-adherent (e.g., ≥4 h of use per night [23]), allowing for clinically interpretable group comparisons. To promote participant retention and complete follow-up, study assessments are scheduled in alignment with routine clinical visits where feasible.

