### 2.7. Data Analysis Plan

Descriptive statistics will be used to summarize demographic and clinical characteristics. The normality of continuous variables will be assessed using visual inspection (Q–Q plots, histograms) and statistical tests (e.g., Shapiro–Wilk). Continuous variables will be presented as mean ± SD for normally distributed data or median with interquartile range for non-normally distributed data. Categorical variables will be expressed as frequencies and percentages.

Primary analyses will evaluate within-subject changes in cognitive function over the 12-month period (i.e., change scores ΔT12–T0). These changes will be analyzed using linear mixed-effects models with a random intercept, which allow for repeated measurements and account for inter-individual variability. Fixed effects will include time, PAP adherence, and covariates such as age, sex, and education. An interaction term between time and adherence will be used to assess whether longitudinal changes differ according to adherence level.

Secondary analyses will explore associations between changes in cognitive outcomes and other measured variables, including sleep parameters, volumetric measures, anthropometric and metabolic indicators, biomarkers, and other selected laboratory measures (e.g., pNfL, ApoE genotype, gut microbiome composition), as well as indices of vascular health and autonomic nervous system function. These associations will be examined using Pearson or Spearman correlations between change scores (ΔT12–T0) and multiple linear regression models with a limited number of predictors (maximum of 4 per model) to minimize the risk of overfitting.

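### Read literally, the data rule for participants who stop PAP leaves early stoppers with a baseline cognitive score and no 12-month score, and so depletes the low end of the adherence exposure

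*Protocol article*

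**What the plan says.** Section 2.8 gives one rule for two groups: "Participants who discontinue PAP therapy or deviate from the protocol will remain in the analytical sample". On what these participants then contribute, the same sentence goes on to state that "all data collected up to the time of discontinuation, including cognitive, clinical, and physiological measures, will be included in the analyses". The only discontinuation it names is that of PAP.

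The Abstract plans that "All participants will undergo comprehensive assessments at baseline and after 12 months", and Table 1 places neuropsychological testing at T1 (baseline) and T3 (12 months) and nowhere between. Section 2.5.1 defines the longitudinal outcome "longitudinally as change in cognitive performance from baseline to 12 months".

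Section 2.7 says: "Primary analyses will evaluate within-subject changes in cognitive function over the 12-month period (i.e., change scores ΔT12–T0", using a random-intercept mixed model. It adds: "An interaction term between time and adherence will be used to assess whether longitudinal changes differ according to adherence level". On the exposure, Section 2.5.3 says: "Adherence will be primarily analyzed as a continuous variable (e.g., average hours of use per night) to capture potential dose–response relationships". A cut at 4 hours per night is the secondary version.

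Section 2.2 states that PAP follows routine care and that the study neither starts, changes nor stops it.

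**The concern.** There is no cognitive score between baseline and month 12. A limit at the moment PAP stops therefore removes the follow-up score of everyone who stops early. Such a participant is retained in name, but a baseline-only record carries almost no information on the 12-month change or on how that change varies with hours of use.

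In an observational cohort whose exposure is hours of PAP, stopping is a low exposure value. It is not in itself a reason to end the use of a participant's data. A rule that drops outcomes at that point thins the part of the exposure range that a dose–response analysis most needs. It also sits badly with Section 4, which relies on stratified and regression analyses by adherence level to deal partly with variable use.

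**Working it through.** **1. The plan's own figures.** Section 2.6 gives d = 0.5, two-sided α = 0.05, 80% power, 34 participants, and 40 after 15% attrition. It also gives f² = 0.15, up to four predictors, 15% attrition and a target of about 100.

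- Paired t-test: noncentrality d√n = 0.5 × √34 = 2.92 with 33 df gives power 0.808. Then 34 / 0.85 = 40.
- Overall F-test of four predictors: noncentrality f²n = 0.15 × 85 = 12.75 with 4 and 80 df gives power 0.803. Then 85 / 0.85 = 100.

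All three stated totals (34, 40, 100) reproduce. With 100 recruited and 15% lost, 100 × 0.85 = 85 have a 12-month score.

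**2. The literal rule applied.** The article gives no PAP stopping rate. I assume 10% to 40%, on top of the 15% attrition. The number with a 12-month score is 85 × (1 − stopping rate), rounded down. Power uses the formulas in step 1 with n replaced.

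| Stop PAP early (assumed) | With a 12-month score | Four-predictor model, f² = 0.15 | Paired test, d = 0.5 |
|---|---|---|---|
| 0%, or stoppers' scores kept | 85 | 0.80 | 0.995 |
| 10% | 76 | 0.75 | 0.990 |
| 20% | 68 | 0.69 | 0.982 |
| 30% | 59 | 0.61 | 0.965 |
| 40% | 51 | 0.53 | 0.938 |

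The bare pre-post test is hardly touched. The multivariable model, whose requirement reproduces the target of 100, is.

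**3. Narrowing of the exposure (illustration).** All usage figures here are assumptions: continuers average 5 h (SD 1.5), and stoppers' 12-month average is 0 to 60% (mean 30%) of what they would otherwise have used. The adherence coefficient is set at f² = 0.15 in the full 85, within a four-predictor model. With the slope and residual variance held fixed, f² shrinks with the variance of hours: f² retained = 0.15 × (SD of continuers / SD of all)².

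| Stop early | SD of hours, all | SD, continuers | f² retained | Power, all 85 | Power, stoppers dropped |
|---|---|---|---|---|---|
| 10% | 1.79 | 1.49 | 0.104 | 0.94 | 0.79 |
| 20% | 1.99 | 1.49 | 0.085 | 0.94 | 0.66 |
| 30% | 2.11 | 1.49 | 0.075 | 0.94 | 0.54 |
| 40% | 2.17 | 1.49 | 0.071 | 0.94 | 0.46 |

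**4. Bias.** If missingness depended only on recorded hours, and the relation with hours were truly linear, the adherence slope would lose precision but not validity. Neither condition is assured. People may stop for reasons linked to their cognitive course, and the few remaining low users would have to stand in for those who stopped. The mixed model's missing-at-random assumption does not clearly repair this. The average 12-month change would also describe mainly those who persisted, which the high power of the paired test does not cure.

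**The case against.** The strongest reply is that the sentence is one of inclusion. It keeps these participants and says that certain data are used. It never says that later data are excluded. It also covers protocol deviators, who have no PAP stop date, so discontinuation could mean leaving the study, which Section 2.3.3 treats separately. The Abstract, Section 2.2 and Table 1 plan the 12-month assessment with no exception for stoppers. This has weight: the exclusion is inferred, and retention may have been the intent. Still, the only discontinuation named is of PAP, the sentence expressly covers cognitive measures, and nothing says that stoppers' 12-month scores are analysed. An analyst following the text could drop them.

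A second reply is that adherence is not the main question. Section 2.1 lists its relation to outcomes among the exploratory aims, and Section 2.6 bases its first calculation on within-subject change. That stands. Adherence nevertheless enters the primary model through its interaction with time in Section 2.7.

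A third is that low users remain. Persistent users under 4 h keep their scores, and participants never prescribed PAP may remain too, although the article does not say how their adherence is coded. This also stands, and step 3's assumptions show it. The share of continuers under 4 h is Φ((4 − 5)/1.5) = Φ(−0.667) = 0.252. At 10% stopping there are 8.5 stoppers and 76.5 × 0.252 = 19.3 low-use continuers. Treating all stoppers as under 4 h, 8.5 / 27.8 = 31% of the non-adherent group is lost. A majority is lost only if stopping exceeds 0.252 / 1.252 = 20%.

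A condensed article may leave coding detail to a fuller document. Here, however, it states a rule, and that rule works against its own analysis.

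**Conclusion.** The concern holds as a defect of wording with real consequences. Taken literally, Section 2.8 leaves early stoppers without a change score, selectively depletes low adherence, and makes missing outcomes depend on the exposure.

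The size rests on an assumed 10% to 40% stopping on top of 15% attrition: four-predictor power falls from 0.80 to between 0.75 and 0.53. The steeper losses in step 3 rest on further assumed usage figures and are only an illustration.

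A reader might infer more: that the article expressly discards later data, that the low end of adherence disappears, that dose–response is the sole primary question, or that power for it collapses. The text does not support the first three, for the reasons given under the objection. As to the last, one scenario (30% stopping, continuers at 5 h with SD 1.3, stoppers near 1 h, 0.125 SD of change per hour, 85 evaluable) does take power from about 0.7 to about 0.25. None of those inputs is in the article, so that fall should not be cited as the size of the problem.

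**What to change.** Reword the sentence in Section 2.8 to say three things:

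- Participants who stop PAP are still assessed at 12 months.
- All their data are analysed, including those collected after stopping.
- Average use is computed over the whole period to the 12-month visit, with nights after stopping counted as zero hours.

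Keep the limit on included data only for participants who leave the study, whether by withdrawing consent or through the physician-led withdrawal in Section 2.3.3. The new text should not make consent withdrawal the only end of data collection, because that would contradict Section 2.3.3.

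This is a data-handling change and leaves clinical management as it is. It adds no visit, since the 12-month assessment is already planned for everyone. The cost is some effort to bring back participants who stopped PAP. It is worth doing soon: Section 3 reports that 12-month assessments are under way, and a score not collected cannot be recovered.

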## 3. Results

At the time of manuscript submission, participant enrolment is ongoing. Baseline and 12-month follow-up assessments are being conducted according to the protocol described above. The planned analyses will evaluate longitudinal changes in cognitive outcomes and their associations with PAP adherence and other physiological parameters.

## 4. Discussion

As the population ages, more adults experience stroke, cognitive impairment, and dementia. Because no effective treatments currently exist to prevent or slow dementia, identifying modifiable risk factors such as OSA is increasingly important [24].

OSA has been linked to substantial cognitive, metabolic, and cardiovascular consequences [3,4,5,6], yet the extent to which these impairments are reversible with long-term therapy remains unclear. By combining a neuropsychological assessment, physiological measures, neuroimaging, and biomarkers, this study provides a systems-level approach to understanding the pathophysiological mechanisms of untreated OSA and the therapeutic potential of PAP therapy.

Previous meta-analytic findings suggest that cognitive impairment in OSA is domain-specific, with the most consistent deficits observed in executive functions, attention, and information processing speed, while other domains such as memory may be less consistently affected. However, the relationship between OSA severity and cognitive outcomes appears heterogeneous and not strictly linear. Methodologically, many existing studies have relied on brief cognitive screening tools and relatively short durations of PAP therapy, which may limit the detection of subtle or domain-specific changes [4]. Complex neuropsychological assessment both before and after intervention may provide stronger empirical support for the connection between OSA and cognitive impairment or reveal new associations. Through PAP treatment, we aim to investigate whether its use is linked to functional brain changes. To our knowledge, no previous study has investigated these relationships with such an extensive multi-modal assessment and controlled set of underlying pathophysiological mechanisms.

This protocol describes a prospective, observational, longitudinal cohort study. The observational design improves ecological validity by reflecting real-world patient characteristics; however, it also introduces methodological limitations that must be considered. Due to the non-randomized design and absence of a placebo or untreated control group, confounding variables cannot be fully eliminated, and causal inferences will be limited. Given the observational design, confounding by indication cannot be excluded. Although PAP therapy adherence will be objectively measured, substantial inter-individual variability in use may limit the interpretability of treatment effects. To partly address this limitation, we will perform stratified and regression-based analyses according to PAP therapy adherence levels, enabling us to explore dose–response relationships while adjusting for relevant covariates. The intentionally restrictive inclusion and exclusion criteria may raise concerns regarding both selection bias and feasibility. While these criteria were designed to reduce the influence of major confounding factors and enhance internal validity, they may result in a more selected study population and limit generalizability. However, based on preliminary analyses of patient flow at the study site, recruitment of the target sample size is considered achievable despite these constraints. The comprehensive nature of the study protocol may increase participant burden; however, the majority of assessments are part of routine clinical practice in the evaluation of patients with OSA.

In summary, this study aims to take a comprehensive approach to understanding how PAP therapy may affect cognition in OSA through an extensive assessment of various physiological and pathophysiological mechanisms. Our findings may inform future intervention strategies and improve our understanding of reversible contributors to cognitive decline.

## 5. Conclusions

This protocol outlines a multimodal observational study designed to examine the relationships between OSA, cognitive dysfunction, and associated physiological and biological mechanisms. The findings may contribute to a better understanding of how PAP therapy and OSA-related pathophysiological processes are associated with cognitive outcomes.

## Figures and Tables

**Table 1 life-16-00692-t001:** Timeline of the study.

Measures	Study Phase			
	T0. Recruiting and Enrollment	T1. Baseline Assessment	T2. Treatment Period	T3. Follow-Up After 12 Months
Informed consent	X			
Demographic data		X		X
Clinical history		X		X
Neurological, pulmonary, and ENT clinical examinations		X		X
Polysomnography		X		X
Neuropsychological assessment		X		X
Brain MRI with volumetry		X		X
Anthropometric measures		X		X
Blood and saliva sampling		X		X
Gut microbiome from stool		X		X
Vascular functions		X		X
Baroreflex sensitivity		X		X
Adherence to PAP therapy (if applicable)			X	X

Abbreviations: ENT—ear, nose, throat; MRI—magnetic resonance imaging; PAP—positive airway pressure.

## Data Availability

The ongoing study includes sensitive clinical data. The data are available from the corresponding author on reasonable request, subject to ethical and institutional restrictions.

## Abbreviations

The following abbreviations are used in this manuscript:

AHI	Apnea-hypopnea index
AI	Augmentation index
ApoE	Apolipoprotein E
BIA	Bioelectrical impedance analysis
BMI	Body mass index
DWI	Diffusion weighted imaging
ENT	Ear, nose and throat
GAD-7	Generalized anxiety disorder 7 item scale
HDL	High density lipoprotein
LDL	Low density lipoprotein
LBP	Lipopolysaccharide binding protein
MoCA	Montreal cognitive assessment
MRI	Magnetic resonance imaging
OSA	Obstructive sleep apnea
PAP	Positive airway pressure
PAT	Peripheral arterial tonometry
PBMC	Peripheral blood mononuclear cells
PHQ-9	Patient health questionnaire 9
pNfL	Plasma neurofilament light chain
PSG	Polysomnography
RHI	Reactive hyperemia index
RT-qPCR	Reverse transcription quantitative polymerase chain reaction
SD	Standard deviation

## Appendix A

**Table A1 life-16-00692-t0A1:** Neuropsychological test battery for the assessment of OSA patients.

Test	Description	Time of Completion
Rey auditory—verbal learning test	A neuropsychological measure of verbal episodic memory, encompassing immediate recall, learning across trials, delayed recall, and recognition. Participants hear a list of 15 words across multiple trials and are asked to recall them immediately and after a delay [25].	15–20 min
Figure copy task	A visuoconstructional task from the Czech short neuropsychological battery. The subject is asked to precisely copy a geometric figure presented on a stimulus sheet. Administered twice (initial and retest) to assess visual perception, spatial planning, and memory [26].	5–10 min
Controlled oral word association test	A verbal fluency task requiring rapid generation of words beginning with specified letters (K—P—S for Slovak population). It assesses phonemic fluency, executive function, and lexical retrieval [27,28].	5 min
Category fluency test	A semantic fluency measure where subjects list as many words from a given category (e.g., animals) in one minute. It evaluates semantic memory and executive retrieval processes [27,28].	5 min
Trail making test	A two-part test evaluating processing speed, visual search, attention, and task-switching. Part A connects numbered dots; Part B alternates between numbers and letters [29].	5–7 min
Stroop color and word test	The stroop color and word test is a widely used neuropsychological measure of selective attention, processing speed, cognitive flexibility, and inhibitory control. In its classic form, participants complete three tasks: word reading, color naming and naming the ink color of color-words printed in an incongruent color (e.g., the word “RED” printed in blue ink), requiring the participant to inhibit the automatic tendency to read the word [30].	5 min
Digit span	A working memory test comprising forward and backward recall of digit sequences. Assesses attention, concentration, and short-term memory [31].	5 min
Montreal cognitive assessment (MoCA)	A 30-point screen for mild cognitive impairment targeting attention, executive function, memory, language, visuospatial abilities, and orientation [32].	10 min
Generalized anxiety disorder 7-item scale (GAD—7)	A 7-item self-report questionnaire to screen and assess the severity of generalized anxiety disorder. Items are rated on a 4-point scale [33].	3 min
Patient’s health questionnaire (PHQ—9)	A 9-item scale assessing depression severity based on DSM-IV criteria. Each item is rated from “not at all” to “nearly every day” [34].	2 min
Total assessment time		60–70 min
